## Abstract

**Background:**

Universal tobacco-prevention programs targeting youths usually involve significant adults, who are assumed to be important social influences. Commitment not to use tobacco, or to quit use, as a formal contract between an adolescent and a significant adult is a preventive model that has not been widely practiced or explored and has been formally evaluated even less. In this paper, we present the rationale and protocol for the evaluation of the Swedish Tobacco-free Duo program, a multicomponent school-based program the core of which rests on a formal agreement between an adolescent and an adult. The adolescent’s commitment mainly concerns avoiding the onset of any tobacco use while the adult commits to support the adolescent in staying tobacco free, being a role model by not using tobacco themselves.

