## Introduction

Social influences, such as smoking parents, siblings, or friends, are the strongest determinants of smoking initiation in adolescence [1,2]. In practice, one may conceptualize smoking initiation as a socially learned behavior, while the subsequent trajectories leading to escalation or to extinction of smoking behavior are determined by a more complex mixture of reinforcing or weaning factors, including genetics, psychosocial circumstances, and availability of tobacco products [3].

According to Bronfenbrenner’s theoretical frame [4], people in close microenvironments are likely to exert the strongest health-related influences (in this case pro or antismoking), at least in early adolescence and during initial episodes. Peers normally exert a direct and proximal influence by creating the context for smoking to occur; in fact, the association of friends or siblings smoking is in many cases stronger than that of parents smoking [5]. Adult influences, on the other end, are conveyed on a broader frame. First, adults may shape opinions and attitudes over developmental years by simply tolerating or not explicitly disapproving of smoking [6]. Smoking behavior among significant adults may further encourage the onset of smoking in adolescence by creating an implicitly favorable norm [7]. Availability of cigarettes with or without permission is high in environments where adults smoke [8], which is an important facilitating factor when purchase is not affordable as it is the case among adolescents, a price sensitive group [9]. Also, the possibility that early exposure to environmental smoking primes the child’s brain to the rewarding properties of nicotine has been presented [10].

Importantly, social influence seems to extend to tobacco uses other than smoking, at least in countries where other established forms of tobacco use exist, as is the case in Sweden, where the use of the oral moist tobacco snus is widespread among men [11].

For these reasons. adult influences (and parents’ influences, in particular) are usually regarded as an important cue in universal prevention of tobacco use.

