The Swedish program *Tobacco-free Duo* is an example of this category of programs, addressing all forms of tobacco use. Details on the intervention and on its preliminary evaluation have been published [22-24]; however, firm conclusions on favorable effects of the intervention could not be reached due to weak study design or to methodologic shortcomings in these earlier evaluations. The Public Health Agency of Sweden commissioned this evaluation in order to strengthen the evidence base to be incorporated in possible future recommendations.

This commission was translated into the following specific objectives: (1) to assess whether the comprehensive Tobacco-free Duo program is superior to an education-only program in preventing onset of use of cigarettes or other tobacco among adolescents or in fostering smoking cessation among smoking parents, (2) to assess whether the adolescents or parents exposed to the core component of the program (adult-child agreement) refrained from using tobacco to a higher extent than those who were only exposed to other components of the program, (3) to explore the impact of the program on the whole school tobacco use prevalence over time, (4) to understand whether receipt of the program entailed negative side effects on the participating adolescents, and (5) to analyze school-level factors related to fidelity of the program implementation.

A health economic evaluation (cost-effectiveness study) will be conducted alongside the randomized controlled trial, and its corresponding protocol will be the object of a separate publication.

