#### Components

In brief, the program aims to mobilize antitobacco practices and attitudes in adolescents’ near environments, with schools as main promoters and arenas for the activities. The recommended starting point is in the sixth or seventh grade of compulsory school (between 12 and 13 years of age), and it encompasses 6 central components that were manualized in this study.

The tobacco-free pair (Duo) core component that is the origin of the program’s name consists of an agreement between an adolescent and a significant adult (at least 18 years old) elected as partner by the adolescents. The pair agrees to remain tobacco free during the following 3 years, at least, until the index adolescent leaves the compulsory school (about 15 years of age). The written agreement is signed by both partners, possibly during a public event in school, strengthening the mutual commitment. However, a pair can be formed anytime during the school year.Student information is given by a member of the school staff who informs the student in the sixth or seventh grade about the school choice to adopt the program, briefly discusses tobacco control issues, and actively encourages participation of the adolescents.Parent information is given during an ordinary parent meeting at school where they are given access to information and materials explaining their role in tobacco prevention and how they can actively support their children in their commitment.As an incentive to participate, all adolescents signing a contract will receive a membership card that entitles them to some fringe benefits in local shops or leisure-time activities.At the end of each school year, the pairs disclose and confirm their tobacco-free status. The disclosure entitles the index adolescent to participate in a lottery taking place just before the summer break.Interactive classroom education is conducted by trained school personnel in all classes during grades 6 (or 7) to 9. This education consists of age-specific information and practical exercises (eg, how to identify and resist social influences). For the purpose of this evaluation, the educational part was further structured and manualized before training personnel.

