**Objective 2**			
	Question 5		Is the probability of having refrained from using cigarettes or any tobacco by the end of follow-up higher among adolescents and parents who smoke who signed the formal agreement to become a tobacco-free pair (core component) compared to those who only received other components?
	Question 6		Is the proportion of sustained quitters (no smoking in the past 30 days) among parents who smoke before the program’s start higher when the index child attended a Tobacco-free Duo school compared to an education-only school, at the end of the compulsory grades?

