**Nonexperimental**			
	**Effect of adhering to the core component *child-adult contract***		
		Population 1	Adolescents participating the longitudinal assessment of the cluster randomized trial
		Intervention	Signing an adult-child contract (as treated)
		Comparator	Receiving other intervention components, no contract (as treated)
		Outcome	Never smoked or used tobacco at follow-up in ninth grade
		Population 2	Parents of adolescents participating the longitudinal assessment of the cluster randomized trial, baseline smokers
		Intervention	Signing an adult-child contract
		Comparator	Receiving other intervention components, no contract
		Outcome	No past 30-day smoking at follow-up

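### Parents in the contract (as-treated) comparison are scored on smoking only, so the any-tobacco part of Question 5 has no parent outcome

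*Protocol article*

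**What the plan says.** All references are to the protocol article.

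- **Objective 2 (Introduction)** asks whether adolescents or parents exposed to the adult-child agreement "refrained from using tobacco to a higher extent than those who were only exposed to other components of the program".
- **Question 5 (Table 1, Objective 2)** opens: "Is the probability of having refrained from using cigarettes or any tobacco by the end of follow-up higher among adolescents and parents who smoke". The contrast is between those who signed the agreement and those who received only other components.
- **Contract (Methods, Components):** "The pair agrees to remain tobacco free during the following 3 years". The Abstract describes the adult's side as "being a role model by not using tobacco themselves".
- **Table 2, nonexperimental block on the contract.** Population 1 (adolescents) has the outcome "Never smoked or used tobacco at follow-up in ninth grade". Population 2 is "Parents of adolescents participating the longitudinal assessment of the cluster randomized trial, baseline smokers", and its single outcome is "No past 30-day smoking at follow-up".
- **Table 1 footnote:** the any-tobacco category covers snus and e-cigarettes.
- **Introduction:** in Sweden "the use of the oral moist tobacco snus is widespread among men".
- **Table 3:** guardians report their own tobacco use at the same time points as the students. Adults in Duo pairs report cigarettes and snus when a contract is signed.

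**The concern.** The question, the contract and the adolescent outcome in the same block all concern tobacco. The parent outcome concerns smoking alone. A parent who signs, gives up cigarettes and uses snus at follow-up has not kept a tobacco-free agreement, yet counts as a success in the row meant to show what signing achieves. The protocol itself describes snus as common among men in this setting, so such a change of product is foreseeable.

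Part of a stated objective is left without an endpoint for one of its two populations. If this is not settled before analysis, the choice between a smoking and a tobacco endpoint for parents may be made with the data in view.

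**Working it through.** The documents give no figure for this comparison that could be reproduced: no sample size, quit rate or snus rate for parents. The check is therefore a comparison of texts, followed by an illustration with assumed rates.

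**1. Matching question to outcome**

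| Group | What is asked | Outcome in Table 2 | Covered |
|---|---|---|---|
| Adolescents, Question 5 | cigarettes or any tobacco | smoking or tobacco | both parts |
| Parents, Question 5 | cigarettes or any tobacco | smoking, past 30 days | cigarette part only |
| Parents, Question 6 | smoking cessation by assigned school | smoking, past 30 days | fully |

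The gap is in the second line only. Reading the wording of Question 5 as two separate outcomes does not close it: the row then answers the first and leaves out the second. No other parent outcome in the article covers snus or any tobacco.

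**2. What the omission could do to the contrast**

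Let q1 and q0 be the proportions of signing and non-signing parents who do not smoke at follow-up. Let s1 and s0 be the shares of those non-smokers who use snus. Then

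- smoking ratio = q1 / q0
- tobacco-free ratio = q1(1 − s1) / [q0(1 − s0)] = smoking ratio × (1 − s1)/(1 − s0)

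All inputs below are assumptions.

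- **More snus among non-signers.** q1 = q0 = 0.15, s1 = 0.10, s0 = 0.30. Smoking ratio 1.00. Tobacco-free: 0.15 × 0.90 = 0.135 against 0.15 × 0.70 = 0.105, ratio 0.135/0.105 = 1.29.
- **More snus among signers.** q1 = 0.15, q0 = 0.10, s0 = 0. Smoking ratio 1.50. With s1 = 0.25: 0.1125/0.10 = 1.125. With s1 = 0.50: 0.075/0.10 = 0.75. Taking q0 as 0.05 or 0.20, with q1 still 1.5 times q0, gives the same ratios.
- **Equal shares.** With s1 = s0 the factor is 1 and the ratio does not change. The levels still differ: 15% not smoking corresponds to 13.5% tobacco free if the share is 10%, and to 10.5% if it is 30%.

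The smoking outcome alone cannot show which case applies.

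**3. Whether the data exist**

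The guardian questionnaire lists own tobacco use at baseline and at each follow-up, so an any-tobacco outcome needs no new data collection if the form separates products over the past 30 days. The article does not give the item wording and does not say whether the form covers e-cigarettes. The Duo-adult form is tied to contract signing, so it cannot supply the follow-up outcome.

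**The case against.** **In favour of leaving the row as it is.** The comparison is secondary and nonrandomized, and the Data Analysis section already warns that as-treated estimates are open to bias. Table 2 is presented as a summary, the Abstract mentions further adult-level outcomes in general terms, and the raw data are to be collected. These points limit the importance of the matter but do not supply the missing outcome. The article states the question and the outcome explicitly, and the two differ.

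**On labelling.** The sections on nonexperimental design and data analysis attach the contract comparison to question 6, which is a smoking question. By content, however, signers against non-signers is Question 5 in Table 1. Question 6 there compares Duo schools with education-only schools.

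**Stronger readings that a reader might infer, and that the documents do not support:**

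- *The experimental parent row is wrong too.* It is not wrong on this point. Objective 1 in the Introduction, Question 6 and the Table 2 heading all name smoking cessation, so that outcome matches its question.
- *Question 5 cannot be answered for parents.* The cigarette part can.
- *The smoking score hides a real effect of the contract.* It might, but the same reasoning with other assumed rates gives an apparent benefit that is absent for tobacco. No direction is established.
- *Any parent who changes to snus breaks the agreement.* Only a parent who is the contract partner does. The adolescent may choose another adult, and the data collection section provides for partners who are not a parent.

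**Conclusion.** The mismatch is real and confined to the Population 2 row in the nonexperimental block of Table 2. As written, the any-tobacco part of Question 5 and of Objective 2 has no parent outcome, and a signing parent who moves from cigarettes to snus is scored a success. The size and direction of any effect on the comparison are unknown. The ratios shown above (1.29 against 1.00; 1.125 or 0.75 against 1.50; no change with equal shares) illustrate the possibilities and are not estimates. The primary outcome, the student sample size and the randomized parent comparison are untouched. The point should be settled before the parent data are analysed, but it does not threaten the trial's main conclusion.

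**What to change.** In the Population 2 row of Table 2, add a second outcome: no use of any tobacco product in the past 30 days at follow-up. Define it as cigarettes or snus, plus e-cigarettes if the guardian form covers them, in line with the Table 1 footnote. Derive it from the guardian items. Keep the existing smoking outcome for the cigarette part of Question 5. Report, by contract status, the share of parents who stopped smoking but use snus at follow-up.

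Alternatively, if tobacco in general was not intended for parents, restrict the parent part of Question 5 and Objective 2 to smoking and say so.

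Leave Question 6 and the experimental parent row as they are on this point.

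The cost is one more secondary outcome, with somewhat fewer successes than the smoking outcome and so a little less precision. The alternative costs only a change of wording, but gives up any statement on whether signing parents became tobacco free.

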	**Decline in school prevalence of never smokers**		
		Population	Students registered in the grades 7-9 of the schools participating in the experimental study and in the schools serving as external reference during three consecutive years
		Intervention 1	Tobacco-free Duo 6 components (as treated)
		Intervention 2	Educational component of Tobacco-free Duo only (as treated)
		Comparator	Usual education or health promotion
		Outcome	Average point prevalence of never smoking in spring term of each school year

^a^PICO: population, intervention, comparator, outcome.

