**Objective:**

To assess (1) whether Tobacco-free Duo is superior to an education-only program in preventing smoking onset among adolescents and promoting cessation among their parents, (2) whether exposure to core components (adult-child agreement) entails more positive effects than exposure to other components, (3) the impact of the program on whole school tobacco use, (4) potential negative side effects, and (5) school-level factors related to fidelity of the program’s implementation.

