**Objective 3**			
	Question 7		Is the total prevalence of never smokers among students in the grades 7 to 9 declining more slowly over 3 years in Tobacco-free Duo schools compared to education-only schools or schools delivering their usual antismoking programs (external reference group schools)?

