**Experimental**			
	**Superiority of Tobacco-free Duo comprehensive intervention vs education only in preventing smoking/tobacco onset**		
		Population	Adolescents 13 years old at baseline with valid parental consent—average follow-up 38 months
		Intervention	Tobacco-free Duo 6 components
		Comparator	Educational component of Tobacco-free Duo
		Outcome 1	Never smoked (negative answer to the question: Did you ever try smoking, even a few puffs?)
		Outcome 2	Never smoked regularly (negative answer to the question: Did you ever smoke weekly for 3 or more months in a row?)
		Outcome 3	Never used any tobacco (negative answer to both questions: Did you ever try smoking, even a few puffs? Did you try smokeless tobacco?)
		Outcome 4	Never used any tobacco regularly (negative answer to both questions: Did you ever smoke weekly for 3 or more months in a row? Did you ever use snus weekly for 3 or more months in a row?)
	**Superiority of Tobacco-free Duo comprehensive intervention vs education only in determining smoking cessation among participants’ parents**		
		Population	Parents of adolescents participating in the trial who reported smoking at baseline
		Intervention	Signing an adult-child contract
		Comparator	Receiving other intervention components, no contract
		Outcome	No past 30-day smoking at follow-up

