Participating students in schools randomized to Tobacco-free Duo or education only	Paper questionnaire, with information on: Cigarette and snus use (any, current, frequency, quitting) Tobacco use among friends and family members Received education, knowledge and attitudes toward tobacco Recent and current use of alcohol Ever use of illicit drugs General health, physical activity, and sedentary time Perceptions about the contract (if appropriate)	Self-administered in the classroom	Unique study code matched to identity information	Baseline: fall term of school year 1- grade 7 Follow-up 1: end of school year, grade 7 Follow-up 2: end of school year 2, grade 8 Follow-up 3: end of school year 3. grade 9
Guardians of the participating students above	Paper questionnaire, with information on: Sociodemographics Relation with the index child and perception of risks with tobacco use Own tobacco and alcohol use	Self-administered at home	Same code as the index child above	Same time points as above
Adults in Tobacco-free Duo pairs	Paper questionnaire, with information on: Own use of cigarette and snus Perception of own role in the intervention	Self-administered at home	Same code as the index child above	Anytime a contract is signed
All students registered in Tobacco-free Duo schools, education-only schools and reference group schools in grades 7-9	Paper questionnaire, with information on: Ever, regular and recent use of cigarette and snus	Self-administered in the classroom	No identifier (anonymous survey)	Cross-sectional surveys at the end of school year 1, 2 and 3

Figure 1 displays a scheme of the participants’ enrollment and assessments time-points for the experimental part of the study.

Individual data from questionnaires will be optically scanned, and the corresponding electronic files will be stored in a password-protected section of the server at the Department of Global Public Health, Karolinska Institutet. In order to preserve strict confidentiality, this data will be stored without personal identifiers, substituted by a study code unique to each participant. Personal identifiers will be kept in a separate section of the same server, only accessible to 2 members of the study team, responsible for data linkage and follow-up procedures, respectively. Ten years after the study start the personal identifiers will be removed and all information will be kept identified only through the study code.

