On the other side, participants in an experiment (be they organizations or individuals) constitute an imperfect representation of the underlying populations on which the inference should be drawn, because of the numerous selection steps involved in the conduction of an experiment [36]. In this study, we plan to include a comparison group that comprises schools that agreed to participate in annual surveys among all students in the 3 final compulsory grades but did not agree to be randomized to either experimental group. These schools are likely to well-represent the majority of Swedish schools (ie, the subgroup consisting of those that would not adopt the intervention if offered it at the scaling-up stage). By comparing the development over time of tobacco use in these schools with that of schools randomized to the minimal or comprehensive intervention (across a set of school-level characteristics), we aim to infer the added effect of the intervention on decline in tobacco uptake. For instance, if the prevalence of lifetime smoking or tobacco use similarly declines in reference group schools as in the randomized ones, we may project that the impact of a large and intensive dissemination of the intervention (even if effective in the randomized comparison) would be minimal.

Furthermore, we propose the use of qualitative methods and of process data in order to achieve 2 additional objectives. The first objective to be pursued is a deeper understanding of how the conduction of the intervention may differ between school organization characteristics. This knowledge is important in order to judge cluster-level confounding in nonrandomized studies [37]. An additional advantage of such a piece of knowledge would be the possibility to make projections of the potential benefits deriving from the application of the method to large communities with a known distribution of the studied characteristics.

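### Objective 3 concerns whole-school tobacco use, but its only question and its only Table 2 outcome measure never smoking, so snus use without smoking counts as success

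*Protocol article*

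**What the plan says.** The Abstract gives Objective 3 as "the impact of the program on whole school tobacco use". The list of specific objectives at the end of the Introduction words it as "to explore the impact of the program on the whole school tobacco use prevalence over time". Neither version limits it to smoking.

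Table 1 places a single question, Question 7, under Objective 3: "Is the total prevalence of never smokers among students in the grades 7 to 9 declining more slowly over 3 years". The section on the nonexperimental design ties the comparison with the external reference schools to that objective and question. The matching block of Table 2 has one outcome: "Average point prevalence of never smoking in spring term of each school year".

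Table 3 lists what the anonymous survey of all students in grades 7 to 9 asks: "Ever, regular and recent use of cigarette and snus". The Discussion, in an example of how the reference-school comparison could be read, writes "if the prevalence of lifetime smoking or tobacco use similarly declines in reference group schools as in the randomized ones".

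**The concern.** The objective and the outcome meant to answer it cover different behaviours. In many papers smoking and tobacco use are loose synonyms, but this protocol separates them by definition, and it studies a program aimed at every form of tobacco in a country where, as the Introduction notes, snus is common among men.

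If Table 2 is followed as written, the whole-school result says nothing about snus in either direction. A student who has used snus but never smoked adds to the favourable proportion. A lower level of snus use in program schools than in education-only or reference schools leaves the outcome unchanged. The Data Analysis section intends this comparison to indicate the likely impact once the program is released, so the scope of the endpoint affects what can be said about release.

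**Working it through.** **1. How the protocol defines the two outcomes.** In Table 2 the cohort outcomes are set by questionnaire items:

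- Outcome 1: "Never smoked (negative answer to the question: Did you ever try smoking, even a few puffs". One item, on smoking.
- Outcome 3: "Never used any tobacco (negative answer to both questions: Did you ever try smoking, even a few puffs? Did you try smokeless tobacco". Two items, smoking and smokeless.

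Table 1 makes the same split: Questions 1 and 2 are on smoking, Questions 3 and 4 on any tobacco product.

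**2. Which objectives have which outcome.**

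| Part of the evaluation | Never smoking | Any tobacco |
|---|---|---|
| Objective 1, consented cohort (Questions 1 to 4) | yes | yes |
| Objective 2, adolescents by contract status (Table 2) | yes | yes |
| Objective 3, whole schools and reference schools (Question 7) | yes | none defined |

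The objective that is worded purely as tobacco use is the one without a tobacco outcome. The Data Analysis section speaks of prevalence trends for this comparison and names no product, so it does not fill the gap.

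**3. Who is miscounted.** Never smoking is a lifetime measure, which gives four groups:

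| Ever smoked | Ever used snus | Stated outcome | Never cigarettes or snus |
|---|---|---|---|
| no | no | success | success |
| no | yes | success | failure |
| yes | no | failure | failure |
| yes | yes | failure | failure |

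Only the second row differs. A student who smokes first and then moves to snus is in the last row and is a failure under both rules.

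**4. Illustration of size.** There is no figure in the plan to reproduce, and no snus prevalence is given. The one documented input is the control prevalence of never smoking, 0.70, from the sample size section. It is a ninth-grade planning value for the cohort and is borrowed here for whole schools. Assume snus-only use of 0.05 in the comparison schools, and let a share d of students take up snus instead of ever smoking.

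- Never smoking, risk ratio = (0.70 + d) / 0.70
- Never cigarettes or snus: comparison 0.70 − 0.05 = 0.65; program (0.70 + d) − (0.05 + d) = 0.65; risk ratio 1.00

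| d | Never smoking | Risk ratio | Never cigarettes or snus | Risk ratio |
|---|---|---|---|---|
| 0.02 | 0.72 vs 0.70 | 1.03 | 0.65 vs 0.65 | 1.00 |
| 0.05 | 0.75 vs 0.70 | 1.07 | 0.65 vs 0.65 | 1.00 |
| 0.07 | 0.77 vs 0.70 | 1.10 | 0.65 vs 0.65 | 1.00 |

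The never-smoking ratios do not depend on the assumed 0.05. The last row equals the risk ratio of 1.10 that the trial is sized to detect on its primary outcome.

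The opposite case: if snus-only use were 0.03 rather than 0.05 and never smoking stayed at 0.70, the stated outcome would give 0.70 / 0.70 = 1.00, while never cigarettes or snus would give 0.67 / 0.65 = 1.03.

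Partial substitution: for a 3.0-point gain in never smoking, the gain in never cigarettes or snus is 3.0 × (1 − f), where f is the share of averted smokers who take snus. That is 3.0, 1.5 and 0 points for f = 0, 0.5 and 1.

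**5. Can the data support the missing outcome?** Yes for snus, since Table 3 lists both products in the anonymous survey. Not for e-cigarettes: the footnote to Table 1 counts them as a tobacco product, but Table 3 lists no such item for that survey.

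**The case against.** Several points on the other side are sound.

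- The Abstract's Methods paragraph says the observational study was added to compare smoking incidence. Together with Question 7 and Table 2, this makes smoking a consistent choice for that comparison, and rewording Objective 3 would also remove the mismatch. This stands, and the fix allows for it.
- A reader might infer that the trial cannot answer Objective 3. The documents do not support that: the survey collects the snus items, and Table 2 is introduced as a summary. What is missing is a defined outcome, not the data.
- A reader might infer that any program effect on snus would be missed. Outcomes 3 and 4 test any tobacco in the randomized cohort, in the same experimental schools and with stronger causal support. The gap is limited to students outside the consented cohort and to the reference schools.
- A reader might infer that any move from cigarettes to snus is scored as benefit. Step 3 shows that this holds only for students who never smoke at all.
- A reader might infer that the projection to dissemination rests on smoking alone. The Discussion names smoking or tobacco use as alternatives, so it is not confined to smoking, though it gives an example and defines no outcome.
- Every magnitude rests on assumed snus figures, and nothing in the documents indicates that substitution will occur. The Introduction's remark on snus concerns men, not pupils in grades 7 to 9.

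These points narrow the consequences. None supplies an any-tobacco outcome for whole schools or reference schools.

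**Conclusion.** The mismatch is real and goes beyond wording, because it decides what Objective 3 can conclude. The stated outcome counts snus use without smoking as success and cannot show a whole-school or reference-school difference in snus use. The actual effect on the results is unknown. The risk ratios above rest on an assumed level of snus-only use and assumed substitution, and show only that a favourable never-smoking result need not mean less tobacco use. The primary randomized analysis is not affected. Objective 3 is exploratory and its reference-school comparison is observational, so this should be corrected but does not threaten the trial's main conclusion.

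**What to change.** In Question 7 and in the Table 2 block for Objective 3, add never use of cigarettes or snus, taken from the existing anonymous survey items, as an outcome reported alongside never smoking. Refer to both when projecting the impact of dissemination. State that this endpoint does not cover e-cigarettes, so it is narrower than the protocol's own meaning of any tobacco product.

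If only never smoking is to be kept, restate Objective 3 in the Abstract and the Introduction as smoking, and limit its conclusion in the same way.

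The cost is a wording change, one more tabulation and one additional reported endpoint in an exploratory, observational comparison. No new data are needed for snus.
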